Therefore, we hypothesize that the administration of *S. maxima* alone or together with an exercise plan will decrease the body fat percentage and blood lipids while increasing physical function in sedentary elderly patients with excessive body mass in a randomized, double-blind, counterbalanced, crossover, controlled trial. The main objective of our research is to evaluate the independent and synergistic effect of 12 weeks of *S. maxima* intake (compared to placebo), with or without an exercise program on the body composition (body fat percentage, muscle mass percentage, and body mass index (BMI)) in sedentary older adults with excessive body mass. The secondary objective is to test the effects of both interventions in the blood lipid profile, energy intake, physical function, sleep wake patterns, mental health, and inflammation, as well as to analyze the influence of the genetic background in all outcomes in older adults with excessive body mass.

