### 2.2. Interventions

The clinical trial consists of two interventions: (1) supplementation with *S. maxima* (5 g/day) or placebo (5 g/day of a low-calorie saccharine), and (2) an exercise program, during a period of 24 weeks in a randomized, double-blind, counterbalanced, crossover, controlled trial with a 2 × 2 factorial design. Presentation of both supplements will be powder encapsulated in dark capsules of 0.5 g to present the same organoleptic attributes and mask their individual characteristics.

Inclusion in the exercise program intervention will be decided by each participant, who will be randomly assigned to one of the two possible nutritional interventions (*S. maxima* or placebo) categorized into four treatments: an exercise program plus *S. maxima* intake; exercise with placebo administration; *S. maxima* intake without exercise, or placebo supplementation without exercise program (Control). To assess compliance to the supplement intake, a crossover will be conducted for the supplementation interventions.

The first period of treatment will be carried out for 12 weeks, followed by a four-week wash-out period to avoid any possible delayed effect of *S. maxima* in the organism. Finally, a further 12 weeks of treatment for the second intervention groups (Figure 1).

Due to absence of data related to wash-out and treatment periods length, we considered 4 and 12 weeks, respectively, as stated by a systematic review of clinical trials that used spirulina as treatment [22].

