### 2.6. Statistical Methods

Normality and homoscedasticity of variables will be screened by the Shapiro–Wilk and the Levene tests, for each group. The analysis of statistical differences among treatments and time, univariate repeated measures ANOVA with two within-participants (initial and final values), and four inter-participants (treatments) factors will be used. Moreover, basal and post-treatment values will be contrasted by paired *t*-tests. Delta values will be analyzed by one-way ANOVA and Tukey Post-hoc tests (normal distribution and equal variances) and Kruskal-Wallis H and Dunn’s Post-hoc test (non-parametric distribution and unequal variances), with Bonferroni setting for multiple comparisons. Spearman correlations will be run to evaluate the associations among variables. Eventual gen-diet and gen-exercise interactions concerning anthropometric and metabolic outcomes will be assessed by univariate regression analyses. Statistically significance will be set at a *p*-value of 0.05. All statistical analyses will be completed using IBM SPSS package version 23 (SPSS Inc, IBM Company, Chicago, IL, USA) and STATA software (StataCorp, College Station, TX, USA).

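### Synergy is half of the main objective, but no planned test isolates the supplement-by-exercise interaction

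*Protocol article*

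**What the plan says.** The Introduction states the aim: "The main objective of our research is to evaluate the independent and synergistic effect of 12 weeks of" *S. maxima*, compared with placebo and with or without exercise, on body composition. Section 2.2 describes a "crossover, controlled trial with a 2 × 2 factorial design" in which participants are "categorized into four treatments: an exercise program plus *S. maxima* intake; exercise with placebo administration", followed by the two arms without exercise. The supplement is randomised and crossed over. Each participant chooses whether to exercise, and the limitations section acknowledges this.

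Section 2.6 lists these treatment comparisons:
- "univariate repeated measures ANOVA with two within-participants (initial and final values), and four inter-participants (treatments) factors will be used";
- "basal and post-treatment values will be contrasted by paired *t*-tests";
- "Delta values will be analyzed by one-way ANOVA and Tukey Post-hoc tests", or Kruskal-Wallis with Dunn's test where assumptions fail, with a Bonferroni setting.

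The only interactions it names are between gene and diet and between gene and exercise, assessed by regression. These belong to the secondary, genetic objective.

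**The concern.** In a 2 × 2 design, synergy is a departure from additivity: the combined effect exceeds the sum of the two separate effects. That is a single contrast among the four cell means. Once the cells become four unordered levels of one factor, the overall test asks only whether any means differ, and each post-hoc test compares two cells. A difference between the combined arm and control is what two ordinary additive effects produce, so it is not evidence of synergy.

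The trial could therefore complete its stated analysis without a test of synergy, although the Discussion presents the study as the first to examine it. The output could also contain a pattern that resembles synergy when none exists.

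**Working it through.** **1. Does any listed test isolate synergy?** Write the mean changes as C (placebo, no exercise), S (supplement only), E (exercise with placebo) and SE (both). Synergy is the 1-df contrast

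I = (SE − E) − (S − C) = SE − E − S + C.

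- *Tukey or Dunn pairs.* The six are S−C, E−C, SE−C, SE−S, SE−E and S−E. Each involves two cells and I involves four, so none is I.
- *One-way ANOVA or Kruskal-Wallis.* This is a 3-df omnibus test that rejects for any difference among the cells.
- *Repeated measures ANOVA.* With two time points, its group-by-time F is the one-way F on the deltas. In a generated data set both equalled 0.8207, so it adds no separate test.
- *Paired t-tests.* These are before/after tests within one group and compare no arms.

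**2. What do the pairs provide?** S−C and SE−E are the supplement effects without and with exercise. E−C and SE−S are the exercise effects under placebo and supplement. These are simple effects and bear on the independent half of the objective.

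**3. How often would additive effects look like synergy?** The article states no effect size, so the effects are assumed. Inputs: 52 participants (section 2.4), taken as 52 / 4 = 13 per cell. Equal cells are an assumption because exercise is self-chosen. The groups are treated as independent, with normal changes in units of the SD of change. Means are C = 0, S = E = d, SE = 2d, so I = 2d − d − d + 0 = 0. The Tukey 5% critical value for 4 groups and 4 × 12 = 48 df is 3.76, so a pair is significant when it differs by about 3.76 / √13 = 1.04 SD. At d = 0.5 the expected SE−C is 1.0, near that threshold, while S−C and E−C are 0.5, well short of it.

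Simulation results:

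| d (SD) | SE beats C | Only SE beats C | SE beats all three | Interaction contrast rejects |
|---|---|---|---|---|
| 0.3 | 14% | 11% | about 1% | 5% |
| 0.5 | 46% | 34% | 3% | 5% |
| 0.6 | 65% | 45% | 5% | 5% |

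In the opposite case, pure synergy (S = E = 0, SE = 1 SD), SE beats C in 46% of runs. That is the same rate as with additive effects of 0.5 SD and no synergy, so this comparison does not separate the two.

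**4. How precise is the right contrast?** On first-period deltas, Var(I) = 4/13, so the standard error is √(4/13) = 0.55 SD and the 95% half-width is 2.01 × 0.55 = 1.1 SD. The non-centrality is I² × 13/4:
- I = 0.5: 0.81, power 14%;
- I = 1.0: 3.25, power 42%;
- I = 1.5: 7.31, power 75%;
- 85% power needs I of about 1.70 SD.

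Using the crossover, I is the difference in within-person supplement effects between an assumed 26 exercisers and 26 non-exercisers. Its variance is 2(1 − r) × 2/26, where r is the within-person correlation of the two changes. The interaction detectable with 85% power is then 1.20, 1.00, 0.85 or 0.66 SD for assumed r of 0, 0.3, 0.5 or 0.7.

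**The case against.** The strongest reply has four parts.

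- **The objective is not left wholly unanswered.** A reader might infer that the plan gives no answer to its main objective, or that it tests nothing beyond Tukey pairs. Neither is supported. Section 2.6 lists several analyses, and the pairwise tests estimate simple effects of each intervention. The article does not define independent effects as marginal ones averaged over the other factor, so simple effects are a fair reading. This part of the objection stands.
- **Misreading is not certain.** The article states no rule under which a significant combined-versus-control pair would count as synergy. One can say only that the pattern could be misread. The rates in the working depend on assumed effects, equal cells and independent groups. Under a stricter reading, in which the combined arm must beat all three others, the false pattern is rare at these effect sizes. This also stands.
- **A separate analysis plan might add the interaction.** This helps only partly. Section 2.6 does not leave the model open: it fixes a four-level treatment factor and names interactions for genes alone.
- **The correct contrast is imprecise and not fully randomised.** True. This is a reason to report it with its interval and caveats. It does not make pairwise significance a substitute.

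**Conclusion.** The concern holds for the synergy half of the main objective. As stated, every treatment comparison in section 2.6 uses either one four-level factor or a before/after test, and none isolates the supplement-by-exercise interaction. This follows from the structure of the tests and rests on no numerical assumption.

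The size of the risk does rest on assumptions. With additive effects of 0.3 to 0.6 SD and 13 independent participants per group, the combined arm alone beats control in about 11% to 45% of trials without any synergy. The independent half of the objective is partly addressed by the pairwise tests. It should be corrected before analysis, because otherwise a stated main aim has no test.

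**What to change.** In section 2.6, replace the four-level treatment factor with supplement (two levels), exercise (two levels) and their product, and estimate the supplement effect within person from the crossover. Define synergy as (*S. maxima* minus placebo in exercisers) minus (*S. maxima* minus placebo in non-exercisers), and report it with its 95% CI. Also report the supplement effect within each exercise stratum. State that no synergy claim will rest on Tukey or Dunn pairs.

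Two statements should accompany the contrast:
- Exercise is self-chosen, so the contrast compares randomised supplement effects between self-selected groups and is not a fully randomised synergy effect.
- Precision is low: about 14% power for a 0.5 SD interaction and 42% for 1.0 SD on first-period deltas at an assumed 13 per cell, and better with the crossover to a degree that depends on the within-person correlation.

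The change needs no new data or visits. Its cost is a rewritten analysis section, a visibly wide interval, and the need to say that 52 participants may not settle the synergy question.

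### Section 2.6 compares change scores without baseline adjustment and chooses the test from incomplete assumption screens, where one pre-set baseline-adjusted crossover model would serve the randomised supplement contrast better

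*Protocol article*

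**What the plan says.** All the relevant text is in the Protocol article, section 2.6.

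- **Screening:** "Normality and homoscedasticity of variables will be screened by the Shapiro–Wilk and the Levene tests, for each group".
- **Main model:** "univariate repeated measures ANOVA with two within-participants (initial and final values), and four inter-participants (treatments) factors will be used".
- **Change scores, first branch:** "Delta values will be analyzed by one-way ANOVA", followed by Tukey comparisons, when the data are normal and the variances equal.
- **Change scores, second branch:** "Kruskal-Wallis H and Dunn’s Post-hoc test (non-parametric distribution and unequal variances), with Bonferroni setting for multiple comparisons".
- **Within-arm tests:** "basal and post-treatment values will be contrasted by paired" *t*-tests.

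No baseline covariate appears in any of these. Section 2.5 repeats all procedures on days 0, 84, 112 and 196, so each 12-week period has its own initial value. Section 2.2 makes the supplement a crossover factor and leaves exercise to the participant's choice. The section on strengths and limitations acknowledges that choice.

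**The concern.** Three features of section 2.6 work against a clean estimate of the supplement effect.

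1. A raw change score subtracts the baseline with a coefficient of exactly 1. Unless baseline and final values are almost perfectly correlated, this carries baseline noise into the comparison. A baseline covariate removes it using data already collected.
2. The test for each outcome is chosen from screening tests on the same data. The rule is also incomplete. It gives no test for normal data with unequal variances, or for non-normal data with equal variances, so an analyst would have to choose after seeing the data.
3. Unequal variances lead to Kruskal–Wallis. That test needs groups of the same distribution under the null, so it does not solve the problem that triggers it.

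At stake are precision in a trial of 52 people and an analysis that is not fixed in advance for each outcome.

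**Working it through.** **Inputs.** N of at least 52, alpha 0.05 and power 0.85 (section 2.4); visits on days 0, 84, 112 and 196 (section 2.5); four treatments (section 2.2). The baseline–final correlation ρ, the SDs and the cell sizes are not given, so every value below is an assumption. ρ cannot be recovered from the sample size either. For the four-group by two-time interaction, 52 participants at 0.85 power fit an effect size f of 0.358 at ρ = 0, 0.253 at ρ = 0.5 or 0.16 at ρ = 0.8.

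**Step 1: two named analyses, one test.** With two time points, the treatment-by-time sum of squares is half the between-group sum of squares of the deltas. Its error term is half the within-group sum of squares. The halves cancel, so F is identical on 3 and N − 4 degrees of freedom. A numerical check with four groups of 13 gave F = 2.0876 both ways.

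**Step 2: between-participant precision.** With equal baseline and final SDs, the variance of a delta is 2σ²(1 − ρ) and the baseline-adjusted variance is σ²(1 − ρ²). The ratio is (1 + ρ)/2.

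| ρ | Variance ratio | Reduction in SE | 52 × ratio |
|---|---|---|---|
| 0.5 | 0.75 | 13.4% | 39.0 |
| 0.7 | 0.85 | 7.8% | 44.2 |
| 0.9 | 0.95 | 2.5% | 49.4 |

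**Step 3: within-participant precision.** Let A be the difference between the two period-final values (days 84 and 196) and B the difference between the two period baselines (days 0 and 112). Let V be their common variance and C their covariance, in units of σ². Differenced deltas have variance 2V − 2C. Regressing A on B leaves V − C²/V. The ratio is (V + C)/(2V).

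- Equal correlations at all visits: C = ρ − ρ − ρ + ρ = 0, ratio 0.50 at any ρ.
- Correlation decaying as ρ^(days/84): V = 2(1 − ρ^(112/84)) and C = 2ρ − ρ^(28/84) − ρ^(196/84).

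| ρ at 84 days | V | C | Ratio |
|---|---|---|---|
| 0.5 | 1.206 | 0.008 | 0.50 |
| 0.7 | 0.757 | 0.077 | 0.55 |
| 0.9 | 0.262 | 0.0525 | 0.60 |

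The variance falls by about 40–50% relative to differenced deltas.

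**Step 4: the selection rule.** Four Shapiro–Wilk tests and one Levene test, each at 5%, are applied to truly normal, equal-variance data. If any failed screen triggers the rank test, 1 − 0.95⁵ = 22.6% of outcomes are diverted. On the literal wording ("non-parametric distribution and unequal variances") the figure is about (1 − 0.95⁴) × 0.05 = 0.9%; simulation gave about 1.3%. The wording does not settle which reading applies.

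**Step 5: false-positive rate of Kruskal–Wallis at nominal 5% (simulated, assumed cells).**

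| Setting | SD ratio 2 | SD ratio 3 |
|---|---|---|
| Cells 18/18/8/8, small cells more variable | 8–9% | 11–12% |
| Cells 18/18/8/8, large cells more variable | below 3% | below 3% |
| Equal cells | 5–6% | about 6% |

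In the first setting at SD ratio 2, the full pre-test procedure (any failure diverts) gave 10.5%, plain ANOVA 14.5% and a Welch test 5.6%. With four cells of 13 the procedure gave 5.1% with equal SDs and 5.7% at SD ratio 2.

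**Step 6: the exercise contrast.** Assume no true effect, a baseline gap of 0.5 SD between choosers and non-choosers, and ρ = 0.8. If the gap is a stable group difference, deltas have no bias and adjustment adds (1 − 0.8) × 0.5 = 0.10 SD. If people select on their baseline value, deltas are biased by −0.10 SD and adjustment is unbiased.

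**The case against.** **Unadjusted deltas are not wrong.** For the randomised supplement contrast they are unbiased, so the case for adjustment is efficiency. This stands. If body fat percentage and BMI correlate at 0.9 or more over 12 weeks, the between-participant gain in SE is at most about 2.5%.

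**The (1 + ρ)/2 ratio is a parallel-group result.** It does not describe a crossover model. This also stands, which is why step 3 is calculated separately.

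**Ignoring the pairing may matter more.** In simulations with a 0.5 SD effect and a correlation of 0.3 between a person's two deltas, treating the deltas as independent gave 1.7% type I error and 0.74 power. A within-participant analysis gave 4.6% and 0.84. With uncorrelated deltas the two were alike (0.71 and 0.70). The covariance structures in step 3 imply zero or slightly negative delta correlation, so the two sets of gains should not be added. Either way, the model must contain the participant.

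**A separate analysis plan may hold more detail.** It may, but section 2.6 itself names the tests and the rule for choosing between them.

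**Stronger readings that the documents do not support:**

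- A reader might infer that the plan generally inflates false positives. It does so only with unequal cells whose smaller members are more variable. Self-selected exercise makes unequal cells possible, but no cell sizes or SDs are given.
- A reader might infer that nearly a quarter of well-behaved outcomes will go to rank tests. That needs the any-failure reading.
- A reader might infer that the paired *t*-tests will stand as evidence against placebo. Section 2.6 only lists them beside the between-treatment tests. Disagreement rates for two independent paired tests do not carry over either, because the supplement and placebo conditions are observed in the same people.

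**Conclusion.** The point holds in a limited form, as a recommended change rather than a fatal flaw. Section 2.6 analyses unadjusted change under two names that amount to one test. It selects the method by a rule that leaves two of four cases open, and it uses Kruskal–Wallis as a remedy for unequal variances, which it is not.

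For the supplement contrast, adjustment saves between 5% (ρ = 0.9) and 25% (ρ = 0.5) of the between-participant variance. It saves about 40–50% of the within-participant variance relative to differenced deltas. Both ranges rest on assumed correlations and equal SDs. Kruskal–Wallis error of about 8–12% is a scenario; with equal cells it stays near 5–6%.

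It would be tempting to call the adjusted model more valid throughout. Step 6 shows why that fails for exercise: neither deltas nor baseline adjustment is unbiased in general when participants choose their group. Nor would an ordinary equal-variance adjusted model cure unequal spread without robust errors.

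**What to change.** Reword section 2.6 before any outcome data are seen:

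1. For the supplement effect, analyse each period's final value (day 84 or 196) with that period's baseline (day 0 or 112) as covariate. Use a mixed model with a participant effect, period, sequence, supplement, exercise and supplement-by-exercise.
2. Use robust standard errors, and fix in advance a log transform of final and baseline values for the skewed markers (TG, IL-6, TNF-α).
3. Delete the Shapiro–Wilk and Levene switch. Let this model replace both the repeated-measures ANOVA and the delta ANOVA or Kruskal–Wallis comparison.
4. Report within-arm changes as means with confidence intervals, without tests.
5. Label the exercise contrast as non-randomised and interpret it accordingly, whichever adjustment is used.

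The cost is a rewritten paragraph. No extra participants, visits or measurements are needed.

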### 2.7. Ethics

Participants will be informed of the study rationale as well as all procedures. Their inclusion will be formalized by signing an informed consent (Supplementary File 3), being anonymity and confidentiality carefully enforced, and all participants data will be stored during five years after the study completion. The protocol and procedures have been approved by the Autonomous University of Baja California (UABC) bioethics committee (Supplementary File 4). One UABC scientific committee member and one UABC bioethics committee member will have always access to the interim results and can decide to terminate the trial according the adverse events or unintended effects that could be presented during trial conduct. The clinical trial has been registered prospectively at ClinicalTrials.gov database (Date of approval: 10 December 2020; Identification number: NCT04658875), moreover, the World Medical Association’s Declaration of Helsinki guidelines [36] will be followed.

## 3. Discussion

The SIE study will be the first examining the synergistic effect of *S. maxima* intake and exercise on adiposity, physical function, serum lipids, mental health, sleep-wake patterns and inflammation, as well as to analyze the influence of the genetic background in these outcomes in older adults, using a double-blind, randomized, crossover trial. Because of the double-blind design, the described methodology and a higher number of participants than other studies [22], it is expected to achieve better support for the hypothesis that *S. maxima* will have hypolipidemic effects and improve on adiposity and physical function together with an exercise program in sedentary older adults with excessive body mass. It is noteworthy that not every overweight or obese patient has problems with lipid metabolism. The association between increase of body fat and lipid alterations is well known [37]. For that reason, the primary focus of this protocol is prevention, which is why we do not consider dyslipidemia as an inclusion criterion even though it could be present in this condition. Finally, it is known that the practice of exercise and a balanced diet stimulate the reduction of body mass in obese people and generally decreases cardiometabolic risk factors, so it probably generates an increase in physical capacity [38]. However, apparently no studies on the decrease in metabolic oxidation by Spirulina’s administration in elder individuals with excessive body mass have been performed. Hence, well-designed studies are needed to examine the therapeutic value of *S. maxima* supplementation in clinical practice and its synergetic effect with or without exercise to reduce dyslipidemias and body fat in overweight and obese people, a fact almost unknown lately [39]. This establishes that the importance of this study is to contribute in the advancement in the frontiers of knowledge.

